# XELOX combined with sintilimab and hyperbaric oxygen therapy for advanced or metastatic gastric/gastroesophageal junction adenocarcinoma: study protocol for a prospective, single-arm, phase Ib/II clinical trial

**DOI:** 10.3389/fimmu.2025.1672725

**Published:** 2026-01-12

**Keywords:** gastric neoplasms, hyperbaric oxygenation, immunotherapy, clinical trial, protocol

## Abstract

**Background:**

Gastric and gastroesophageal junction cancer (GC/GEJC) is the fifth most common and deadliest cancers worldwide, with five-year survival rates ranging from 20–40% due to late-stage diagnosis. First-line treatment for HER2-negative advanced or metastatic GC/GEJC involves chemotherapy combined with PD-1 inhibitors, achieving an objective response rate (ORR) of approximately 60%. However, primary and acquired resistance limits effectiveness, highlighting the need for novel strategies. Tumor hypoxia reduces the efficacy of immune checkpoint inhibitors (ICIs). Hyperbaric oxygen therapy (HBOT) may alleviate hypoxia, enhance drug delivery, and improve immune cell infiltration, potentially increasing the antitumor effects of ICIs.

**Methods:**

This prospective, single-center, single-arm phase Ib/II trial evaluated the efficacy and safety of the XELOX regimen combined with sintilimab and HBOT in HER2-negative advanced or metastatic GC/GEJC patients. Phase Ib employs a 3 + 3 dose-escalation design with nine patients to assess safety and determine the optimal HBOT protocol. Phase II will enrol 48 patients, accounting for a 5% dropout rate, with a focus on the ORR as the primary endpoint. The secondary endpoints include progression-free survival (PFS), the disease control rate (DCR), 2-year disease free survival (DFS), two-year overall survival (OS), quality of life (QoL), and safety. All participants received XELOX, sintilimab and HBOT. Efficacy is assessed every two cycles, with maintenance therapy continuing until disease progression or other termination criteria are met.

**Discussion:**

This is the first clinical trial to explore the efficacy and safety of HBOT combined with chemotherapy and immunotherapy in HER2-negative advanced or metastatic GC/GEJC patients. These results may provide a novel treatment strategy for patients with advanced GC/GEJC, addressing the current limitations of immunotherapy resistance.

**Clinical Trial Registration:**

ClinicalTrials.gov, identifier NCT06742411.

## Trial registration details

The clinical trial is registered at ClinicalTrials.gov (Identifier: NCT06742411) and conforms to the World Health Organization Trial Registration Data Set. The schedule of enrolment, interventions, and assessments is illustrated in **Figure 1**. This study is conducted in accordance with Protocol Version 1.3, dated 31 October 2024. Participant recruitment began on 31 December 2024 and is expected to be completed by approximately 31 December 2026.

**Figure 1 f1:**
[figure not shown]
SPIRIT figure. SPIRIT showing the schedule of enrollment, interventions, and assessments in the Phase Ib/II single-arm trial evaluating XELOX, sintilimab, and HBOT in patients with HER2-negative advanced or metastatic GC/GEJC. The timeline encompasses initial screening procedures and baseline data collection, followed by six 21-day cycles of therapy in which oxaliplatin and sintilimab are administered intravenously on Day 1 of each cycle, capecitabine is given orally on Days 1–14 of each cycle, and HBOT at 2.0 atmospheres absolute for 60 minutes is delivered on Day 1 after the drug infusions. After completing six cycles, patients transition to a maintenance phase with capecitabine and sintilimab only. Radiologic tumor evaluations are performed every two cycles until disease progression, and biomarker specimens are collected at predefined time points, including an optional tumor biopsy at progression. Throughout the study, each cycle includes pre-treatment laboratory tests, tumor marker measurements, and ECOG performance status assessments, and all adverse events are closely monitored.

## Introduction

Gastric cancer (GC) is the fifth most common and deadly malignancy worldwide. In 2022, there were approximately 960,000 new cases of GC/GEJC globally, resulting in over 650,000 deaths (1). The primary treatment for GC involves surgical intervention via a multidisciplinary approach. However, owing to its often insidious onset, most patients are diagnosed at a stage with distant metastasis, leading to an overall poor prognosis, with five-year survival rates ranging from 20% to 40% (2). For these patients, chemotherapy-based medical treatment remains the main therapeutic strategy. In recent years, immune checkpoint inhibitors (ICIs) have been successfully applied in various cancers. In the treatment of GC/GEJC, several phase III clinical trials, including CheckMate-649, Orient 16, and Rationale 305, have demonstrated that, compared with chemotherapy alone, combining PD-1 inhibitors with chemotherapy significantly improves progression-free survival (PFS) and overall survival (OS) (3–5). On the basis of these findings, multiple guidelines recommend chemotherapy combined with PD-1 inhibitors as first-line treatment for HER2-negative advanced or metastatic GC. However, the objective response rate (ORR) for PD-1 inhibitors combined with chemotherapy is only approximately 60%, indicating that many GC/GEJC patients do not benefit from PD-1 inhibitor therapy because of primary resistance (3). Additionally, some patients who initially respond may experience relapse, reflecting acquired resistance (6). Therefore, there is an urgent need for new therapeutic strategies in clinical practice to further increase the efficacy of immunotherapy.

Hypoxia is a common feature of most solid tumors and is one of the mechanisms limiting the efficacy of ICIs within the hypoxic tumor microenvironment (7). Hypoxia activates the hypoxia-inducible factor-1 (HIF-1) signaling pathway, increasing the expression of collagen genes and connective tissue growth factor (CTGF), thereby promoting collagen synthesis and the formation of a dense extracellular matrix (ECM) (8). The abnormal ECM and inherent stress generated by tumor growth compress the tumor’s blood and lymphatic vessels, reducing tumor perfusion and impairing drug delivery to the tumor tissue. This creates a physical barrier against ICIs and cytotoxic T lymphocytes (CTLs), thereby diminishing the efficacy of ICIs (9, 10). In addition to causing an abnormal ECM, hypoxia affects CTL function by cultivating an immunosuppressive microenvironment through various pathways. First, hypoxia directly upregulates the expression of programmed death-ligand 1 (PD-L1), leading to the depletion and inhibition of CTL function (11). The hypoxia/HIF-1 axis also promotes the recruitment and accumulation of immunosuppressive regulatory T (Treg) cells, myeloid-derived suppressor cells (MDSCs), and M2 phenotype tumor-associated macrophages (TAMs) (12, 13). These immunosuppressive cells further secrete inhibitory cytokines, collectively coordinating an immunosuppressive microenvironment. Cancer stem cells (CSCs), which are highly proliferative, possess self-renewal capabilities, and have multilineage differentiation potential, have been shown to play significant roles in tumor multidrug resistance, angiogenesis, and invasive metastasis (14, 15). Previous studies have indicated that hypoxia can upregulate the expression of various CSC-related signaling pathway molecules, including Notch, Wnt, and Sonic hedgehog (Shh), and increase the expression of CSC-like proteins (16, 17). Therefore, overcoming tumor hypoxia is crucial for the effective utilization of immune checkpoint blockade (ICB) antibody-mediated immunotherapy.

Hyperbaric oxygen therapy (HBOT), which involves the inhalation of pure oxygen under high pressure, can significantly increase oxygen levels in the blood and tissues and has been widely used to treat various hypoxia-related diseases. HBOT can effectively alleviate tumor hypoxia and is a potent means of reversing the hypoxic tumor microenvironment. Studies have shown that HBOT can reduce collagen deposition through the hypoxia/HIF-1α/CTGF/type I collagen signaling axis and degrade the ECM by generating excessive reactive oxygen species (ROS), thereby promoting drug delivery and CTL infiltration (18–20). Additionally, HBOT can reduce the recruitment of immunosuppressive cells by decreasing the activation of the HIF-1α pathway (18, 21, 22). Moreover, a high-oxygen environment increases the expression of the platelet endothelial cell adhesion molecule CD31, promoting vascular normalization and increasing immune cell infiltration into tumor sites (23). Combining HBOT with chemotherapy can enhance the efficacy of PD-1 antibodies by activating the cGAS-STING signaling pathway, thereby increasing the function of effector T cells and natural killer cells (24). These data suggest that HBOT can significantly increase the efficacy of ICIs and may represent a promising strategy for advanced GC/GEJC.

In this study, we investigated the efficacy and safety of XELOX combined with sintilimab and HBOT in HER2-negative advanced or metastatic GC/GEJC.

## Methods

This is a prospective, single-center, single-arm phase Ib/II clinical trial designed to evaluate the efficacy and safety of XELOX in combination with sintilimab and HBOT in HER2-negative advanced or metastatic GC/GEJC patients. The study protocol and informed consent forms were reviewed and approved by the Academic Review Committee and Ethics Committee of West China Hospital, Sichuan University (WCH20242269). The clinical trial will be conducted in accordance with the Declaration of Helsinki and good clinical practice guidelines. All the participants provided written informed consent, and all the data were kept confidential. No independent committees were established for this single-arm clinical trial. The clinical trial is prospectively registered on ClinicalTrials.gov (NCT06742411).

Phase Ib uses a standard 3 + 3 dose−escalation design to evaluate the safety/tolerability of XELOX plus sintilimab with HBOT and to identify the recommended Phase II HBOT regimen (RP2D). Approximately nine patients are expected in Phase Ib per the 3 + 3 algorithm (no formal power calculation), and Phase Ib enrollment does not contribute to the Phase II power determination.

For Phase II, the sample size is based on the primary endpoint of ORR. Historical first−line data for XELOX plus PD−1 inhibitors suggest an ORR of 58%. Assuming the addition of HBOT increases ORR to 73%, a two−sided α=0.20 and 80% power in an exact single−arm binomial framework yield a required sample size of 45 patients. Allowing for 5% attrition, the planned Phase II enrollment is 48 patients. This calculation is signal−seeking and estimation−oriented rather than confirmatory. Detailed statistical methods are described in the Statistical Analysis section.

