#### Efficacy endpoints

This is a single-arm exploratory trial; therefore, all efficacy results will be descriptive with no formal between-group comparisons. The primary efficacy endpoint for Phase II is the ORR, defined as the proportion of patients achieving a best overall response of CR or PR as determined by investigator assessment according to RECIST v1.1. The first tumor assessment is scheduled at approximately 6 weeks of therapy, which corresponds to the end of two treatment cycles. ORR will be reported along with a two-sided 95% exact confidence interval calculated using the Clopper–Pearson method. In the ITT analysis, patients with no post-baseline tumor assessments will be considered non-responders for the purpose of calculating ORR. The observed ORR will be compared qualitatively to historical outcomes from first-line therapy for advanced GC/GEJC; however, no formal hypothesis testing will be performed due to the single-arm study design.

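### The Phase II size of 45 is a normal-approximation result, not an exact one, and raising it to 48 for 5% attrition does not protect power under the ITT non-responder rule

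*Protocol article*

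**What the plan says.** The Phase II sample-size paragraph (protocol article, Methods) sets a historical response rate of 58%, a hoped-for rate of 73%, "two−sided α=0.20" and 80% power. It attributes the result to an exact single-arm calculation: "binomial framework yield a required sample size of 45 patients. Allowing for 5% attrition, the planned Phase II enrollment is 48 patients". The Abstract repeats the allowance: "Phase II will enrol 48 patients, accounting for a 5% dropout rate". The same Methods paragraph describes the calculation as exploratory and aimed at estimation, not confirmation.

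Under Analysis populations, the ITT set is everyone who consented and received any study treatment, and it is the main set for efficacy. Under Efficacy endpoints: "In the ITT analysis, patients with no post-baseline tumor assessments will be considered non-responders for the purpose of calculating ORR". The Missing data section repeats that rule. Efficacy endpoints also places the first scan at about six weeks, reports the ORR with a 95% Clopper–Pearson interval, compares it only qualitatively with historical results, and rules out a formal test.

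**The concern.** Two statements in the article do not fit the rest of it.

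First, a reader who applies the stated method does not obtain the stated number, because exact binomial power at 45 is below 80%.

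Second, dividing 45 by 0.95 makes sense when lost patients drop out of the analysis and about 45 evaluable patients remain. Under the ITT rule, a treated patient lost before the first scan stays in the denominator as a non-response. That loss lowers the response rate itself, and a few extra enrolments do not offset it.

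Alpha and power are the only justification given for 48 patients. If the observed ORR looks unremarkable, readers will weigh it against a claimed 80% chance of seeing a 15-point gain. If the real chance is lower, a null-looking result is weaker evidence against the combination than it appears.

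**Working it through.** **Inputs.** p0 = 0.58, p1 = 0.73, two-sided alpha 0.20 (0.10 in the upper tail), power 80%, attrition 5% (all from Methods). The ITT definition is from Analysis populations, and the non-responder rule is from Efficacy endpoints and Missing data.

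**Reproducing 45 and 48.** The one-sample normal approximation is

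n = [(z₀.₉₀·√(p0(1−p0)) + z₀.₈₀·√(p1(1−p1))) / (p1−p0)]²

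= [(1.2816·√(0.58·0.42) + 0.8416·√(0.73·0.27)) / 0.15]² = 44.99, rounded up to 45.

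Then 45/0.95 = 47.4, rounded up to 48. Both stated figures reproduce, but 45 does so by the approximation.

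**Exact calculation.** Take the smallest r with P(X ≥ r | n, 0.58) ≤ 0.10; power is P(X ≥ r | n, 0.73).

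| n | r | one-sided alpha | power |
|---|---|---|---|
| 45 | 31 | 0.0905 | 78.8% |
| 46 | 32 | 0.0733 | 75.9% |
| 47 | 33 | 0.0589 | 72.9% |
| 48 | 33 | 0.0850 | 79.8% |
| 50 | 34 | 0.0975 | 83.1% |

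The first n with at least 80% power is 50. Power rises and falls with n because the cut-off moves in whole patients. A two-sided exact test that orders outcomes by likelihood, at alpha 0.20, first reaches 80% at n = 47 (82.3%) and gives 78.8% at 45. Neither exact version yields 45.

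**Effect of the ITT rule at 48 enrolled.** The article does not say whether 73% is a rate among all treated or among assessed patients, or what kind of loss the 5% covers. Each reading below is therefore an assumption.

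| Assumption | Calculation | Power |
|---|---|---|
| 73% is already the ITT rate | P(X ≥ 33 \| 48, 0.73) | 79.8% |
| All losses precede treatment, so they fall outside ITT; 45 to 47 treated | exact table above | 73–79% |
| Both rates diluted by 5% (0.551 vs 0.6935), r = 32, alpha 0.0701 | P(X ≥ 32 \| 48, 0.6935) | 71.7% |
| 73% among assessed, exactly 2 of 48 treated but unscanned | P(X ≥ 33 \| 46, 0.73) | 64.8% |
| 73% among assessed, 5% treated but unscanned, 58% undiluted | 0.95·0.73 = 0.6935; P(X ≥ 33 \| 48, 0.6935) | 60.5% |
| 73% among assessed, exactly 3 of 48 treated but unscanned, 58% undiluted | P(X ≥ 33 \| 45, 0.73) | 55.7% |

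The range is about 56% to 80%.

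**The case against.** A reader might infer that the trial simply has about 60% power. The article does not support that. The figure needs three conditions that are stated nowhere: every lost patient was treated but never scanned, 73% is a rate among assessed patients, and the 58% benchmark contains no unassessed patients. Reading 73% as the ORR defined under Efficacy endpoints, with unassessed patients already counted as failures, is natural and gives 79.8%. Patients who enrol but never start treatment do leave the ITT set, so an allowance for them is coherent. Patients lost after the six-week scan are not automatically non-responders, so 5% attrition is not the same as 5% unassessed. All of this stands, and 60% can be given only as a conditional scenario.

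It is also fair that the wrong method label costs little by itself: 1.2 points at 45 and 0.2 points at 48.

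Finally, no formal test is planned, so the cut-off of 33 responses is a planning construct and no decision rule is underpowered. That limits the consequence. It does not remove the error, because alpha, power and an exact method are still the stated basis for 48 patients.

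**Conclusion.** The point holds in two parts. The derivation is mislabelled: 45 is the normal-approximation answer, and the exact upper-tail method needs 50 (47 with the likelihood-ordered two-sided test). By itself this is minor.

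The attrition allowance does not match the primary analysis. It offers no protection against treated patients who are never scanned, because the ITT rule turns them into non-responses. Depending on what 73%, 58% and the 5% mean, planning power at 48 lies between about 56% and 80%. It is about 60% only under the three conditions named above. With the upper-tail exact test, no reading examined at 48 enrolled reaches the stated 80%; the highest is 79.8%.

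What is affected is the justification of the sample size, not the validity of the planned estimate or its confidence interval.

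**What to change.** Keep 48 patients and rewrite the sample-size paragraph.

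- Either label 45 as a normal-approximation figure, or replace it with the exact operating characteristics at 48 treated patients: 33 or more responses, one-sided alpha 0.085.
- State power as about 80% if the ITT ORR, with unassessed patients as non-responders, is 73%, and about 60% if 73% applies to assessed patients, 5% are treated but unassessed and the 58% benchmark is undiluted.
- Say whether 73% is an ITT rate and which losses the 5% covers.
- Drop the implication that the 5% inflation preserves 80% power under the ITT non-responder rule.
- Say that the cut-off and power are planning figures and not a decision rule, so that the paragraph agrees with the statement under Efficacy endpoints that no formal test is planned.

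The cost is one reworded paragraph and a less favourable stated power. No extra patients and no change to the analysis are needed.

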### Endpoints

The primary goal of Phase Ib is to assess the safety and tolerability of the XELOX regimen combined with sintilimab and HBOT in treating advanced or metastatic GC/GEJ adenocarcinoma and to determine the optimal HBOT protocol for Phase II.

The primary endpoint of Phase II is the objective response rate (ORR). The secondary endpoints include PFS, DCR, two-year DFS (for patients converted to resectable disease and achieving R0 resection), two-year OS, and quality of life and safety profiles. Adverse events (AEs) will be recorded and evaluated according to the National Cancer Institute Common Terminology Criteria for Adverse Events (NCI CTCAE, version 5.0). Severe adverse events (SAEs) are defined as death, hospitalization or prolonged hospitalization, permanent or severe disability, congenital anomalies, or other significant clinical sequelae.

Exploratory biomarkers will be collected at prespecified timepoints from tumor tissue (CD8^+^ T−cell density; HIF−1α and CAIX), blood (CD4%, CD8%, and the CD4:CD8 ratio), and fecal samples (Shannon diversity index); analyses are descriptive and hypothesis−generating, as detailed in **Supplementary File 1**. Samples will be processed and stored in a secured biobank following standard operating procedures. Any future research using stored samples will require separate ethical approval.

### Study population and eligibility criteria

#### Inclusion criteria:

Diagnosis: Histologically or cytologically confirmed adenocarcinoma of the stomach or gastroesophageal junction (including signet ring cell carcinoma, mucinous adenocarcinoma, and hepatoid adenocarcinoma).Disease status: The presence of metastatic disease, attributable to either recurrence or distant dissemination, was established through a combination of radiologic or surgical assessments.Survival Expectancy: Predicted to live more than 3 months.Age: 18–75 years.Prior treatments:There are no previous antitumor treatments (chemotherapy, radiotherapy, targeted therapy, immunotherapy, interventional therapy, etc.).If patients previously received adjuvant or neoadjuvant therapy, the last treatment must have been completed at least 6 months before enrollment, with no recurrence or disease progression during treatment.Palliative radiotherapy is allowed if it is completed at least 2 weeks before the first study treatment.The use of prior anti-tumor traditional Chinese medicine is allowed if it is discontinued at least 2 weeks before enrollment.Performance Status: ECOG PS ≤1.Assessable lesion: At least one measurable lesion per the RECIST 1.1 criteria.Pathological samples: Patients whose archived or fresh pathological tissue was obtained within 6 months before signing informed consent, which was sufficient for PD-L1 testing with obtainable results, were included.Organ function:Hematology (no transfusion or G-CSF use within 14 days before screening):Hemoglobin ≥90 g/L.Absolute neutrophil count (ANC) ≥1.5×10^9^/L.Platelet count ≥75×10^9^/L.Biochemistry (no albumin use within 14 days before screening):Albumin ≥28 g/L.Total bilirubin ≤1.5×ULN.AST and ALT levels were ≤3×ULN (≤5×ULN if liver metastasis was present).Creatinine ≤1.5×ULN.Coagulation:INR or PT ≤1.5×ULN.APTT ≤1.5×ULN.Systemic treatment history: No systemic treatment (including adjuvant/neoadjuvant) was given within the past 6 months after sample collection for enrollment.Toxicity: Prior antitumor treatment or surgery-related acute toxic reactions were resolved to grade 0–1 per NCI CTCAE v5.0 or to levels specified by the inclusion/exclusion criteria.Contraception: Strict contraception measures.Consent and Compliance: Signed informed consent, willing and able to comply with study visits, treatments, lab tests, and procedures.

#### Exclusion criteria:

HER2 status: HER2-positive (HER2 3+ or 2+ & FISH+).Tumor type: Nonadenocarcinoma gastric cancers, including squamous cell carcinoma, undifferentiated carcinoma, or mixed histological types.CNS Metastasis: Uncontrolled or symptomatic active CNS metastasis (e.g., clinical symptoms, brain edema, spinal cord compression, carcinomatous meningitis, soft meningeal disease, or progressive growth).Fluid accumulation: Uncontrolled pleural effusion or ascites treated with drainage within 14 days before enrollment; symptomatic or moderate to large pericardial effusion.Weight loss: Weight loss >20% within 2 months before enrollment.Recent treatments:Major surgery within 28 days before enrollment (diagnostic biopsies and PICC placement allowed).Immunosuppressive drugs should be used within 7 days before enrollment, excluding nasal/inhaled corticosteroids or physiological-dose systemic steroids (≤10 mg/day prednisone or equivalent).Live attenuated vaccines were administered within 28 days before enrollment, during the study, or within 60 days after treatment ended.Antitumor treatments were administered within 28 days before enrollment (chemotherapy, radiotherapy, immunotherapy, endocrine therapy, targeted therapy, biological therapy, or tumor embolization).Other Malignancies: Patients were diagnosed with any other malignancy within 3 years before study entry, except for localized and cured basal cell carcinoma, squamous or superficial bladder carcinoma, cervical carcinoma *in situ*, ductal carcinoma *in situ* of the breast, and papillary thyroid carcinoma.Autoimmune Diseases: Any active, known, or suspected autoimmune disease. Stable conditions not requiring systemic immunosuppression are allowed (e.g., type I diabetes; hypothyroid diabetes managed with hormone replacement; and skin diseases not needing systemic treatment, such as vitiligo, psoriasis, and alopecia).Neurological/Psychiatric Conditions: Uncontrolled epilepsy, congenital spherocytosis, claustrophobia, or angle-closure glaucoma.Immune therapy history: Prior treatment with anti-PD-1/PD-L1 antibodies, anti-CTLA-4 antibodies, or other T-cell costimulation/checkpoint pathway drugs.Bleeding/thrombosis events: significant bleeding symptoms or tendencies within 3 months before enrollment; gastrointestinal perforation or fistula within 6 months; thrombotic events (e.g., stroke, deep vein thrombosis, pulmonary embolism) within 6 months.Major Vascular Disease: Major vascular disease within 6 months before study treatment (e.g., aortic aneurysm needing surgery or recent peripheral arterial thrombosis).Wounds and fractures: Severe, unhealed, or open wounds; active ulcers; or untreated fractures.Neuropathy: Peripheral neuropathy >Grade 1.Intestinal Obstruction: History of intestinal obstruction or related symptoms within 6 months before study treatment. Patients treated surgically to resolve incomplete obstructions at initial diagnosis may be included.Systemic diseases: Interstitial lung disease, noninfectious inflammation, or uncontrolled systemic diseases (e.g., diabetes, hypertension, pulmonary fibrosis, acute pneumonia).Drug Allergies: Patients with known severe allergic reactions to the study drugs or any monoclonal antibodies.HIV/AIDS: HIV infection or known AIDS.Hepatitis: Untreated active hepatitis B (HBV-DNA ≥500 IU/ml), hepatitis C (HCV-RNA above the detection limit), or coinfection with HBV and HCV.Cardiac conditions: Myocardial infarction, severe/unstable angina, NYHA Class II or higher heart failure, significant arrhythmias, or congestive heart failure within 6 months before enrollment.Hypertension: Poorly controlled hypertension despite treatment (systolic BP >140 mmHg or diastolic BP >90 mmHg).Infections and Fever: Systemic antibiotic use ≥7 days within 4 weeks before enrollment or unexplained fever >38.5 °C during screening/before the first dose (tumor-related fever allowed on the basis of the investigator’s judgment).Transplant history: Known history of allogeneic organ or hematopoietic stem cell transplantation.Other Clinical Trials: Participation in any other drug clinical trial within 4 weeks before enrollment or within 5 half-lives of the last study drug.Substance Abuse: History of psychiatric drug abuse or drug addiction.Other Severe Conditions: Any other serious physical or mental illness, abnormal lab tests increasing study risk or interfering with results, or deemed unsuitable by the investigator.Pulmonary conditions including a history of treated pneumothorax, severe emphysema, or pulmonary bullae.
